# Evaluating the Efficacy of a Mobile App (Drinks:Ration) and Personalized Text and Push Messaging to Reduce Alcohol Consumption in a Veteran Population: Protocol for a Randomized Controlled Trial

**DOI:** 10.2196/19720

**Published:** 2020-10-02

**Keywords:** alcohol misuse, smartphone, intervention, SMS text messaging, push notifications

## Abstract

**Background:**

Alcohol misuse is higher in the UK Armed Forces than in the general population. Previous research has shown that interventions delivered via smartphones are efficacious in promoting self-monitoring of alcohol use, have utility in reducing alcohol consumption, and have a broad reach.

**Objective:**

This single-blinded randomized controlled trial (RCT) aims to assess the efficacy of a 28-day brief alcohol intervention delivered via a smartphone app (*Drinks*:Ration) in reducing weekly self-reported alcohol consumption between baseline and 3-month follow-up among veterans who drink at a hazardous or harmful level and receive or have received support for mental health symptoms in a clinical setting.

**Methods:**

In this two-arm, single-blinded RCT, a smartphone app that includes interactive features designed to enhance participants’ motivation and personalized messaging is compared with a smartphone app that provides only government guidance on alcohol consumption. The trial will be conducted in a veteran population that has sought help through Combat Stress, a UK veteran’s mental health charity. Recruitment, consent, and data collection will be carried out automatically through the *Drinks*:Ration platform. The primary outcome is the change in self-reported weekly alcohol consumption between baseline (day 0) and 3-month follow-up (day 84) as measured using the Time-Line Follow back for Alcohol Consumption. Secondary outcome measures include (1) change in the baseline to 3-month follow-up (day 84) Alcohol Use Disorder Identification Test score and (2) change in the baseline to 3-month follow-up (day 84) World Health Organization Quality of Life-BREF score to assess the quality of adjusted life years. Process evaluation measures include (1) app use and (2) usability ratings as measured by the mHealth App Usability Questionnaire. The primary and secondary outcomes will also be reassessed at the 6-month follow-up (day 168) to assess the longer-term benefits of the intervention, which will be reported as a secondary outcome.

**Results:**

The study will begin recruitment in October 2020 and is expected to require 12 months to complete. The study results will be published in 2022.

**Conclusions:**

This study assesses whether a smartphone app is efficacious in reducing self-reported alcohol consumption in a veteran population that has sought help through Combat Stress using personalized messaging and interactive features. This innovative approach, if successful, may provide a means to deliver a low-cost health promotion program that has the potential to reach large groups, in particular those who are geographically dispersed, such as military personnel.

**Trial Registration:**

ClinicalTrials.gov NCT04494594; https://clinicaltrials.gov/ct2/show/NCT04494594

**International Registered Report Identifier (IRRID):**

PRR1-10.2196/19720

## Introduction

### Alcohol Misuse Burden

Alcohol misuse is common in the UK Armed Forces (AF), with the prevalence higher in the AF than in the general population [1-4]. Research indicates that this trend continues after personnel leave service (*veteran* or *ex-serving* is used interchangeably in the UK) [1,5]. It has been estimated that more than 50% of those who have left the AF meet the criteria for hazardous alcohol use, a score of 8 or above on the Alcohol Use Disorders Identification Test (AUDIT) [3,6].

Research has shown that individuals in the general population underestimate their drinking and do not perceive it as problematic, even at potentially harmful levels [7]. Young males are at particular risk of underestimating their drinking [7]. This pattern is similar among the UK AF, with less than half of UK AF hazardous drinkers recognizing that they have an alcohol problem [8]. There is also a culture of heavy alcohol use in the UK AF, which is encouraged by the social environment and carries on after personnel leave service [4,9,10]. Therefore, leaving service could provide an opportunity to initiate behavior change in settings with less peer pressure to conform to social norms and promote alcohol awareness.

Focusing on personnel who have left service, a similar pattern has emerged for those who are seeking support for mental health problems and consume alcohol to cope. A recent study of treatment-seeking UK service leavers identified that 43% of respondents reported misusing alcohol and that alcohol misuse was commonly comorbid with posttraumatic stress disorder (PTSD) and common mental health difficulties such as anxiety and depression [11]. Alcohol misuse can also have an impact on treatment adherence. Treatment-seeking veterans with alcohol misuse attended fewer mental health appointments and were more likely to have a negative perception of mental health treatment when alcohol misuse is comorbid with depression or PTSD [12]. It is, therefore, important to develop interventions that may target drinking to cope with motivations, which may subsequently enhance engagement with mental health services and improve mental health outcomes.

The impact of alcohol misuse by AF personnel on the wider society (eg, health care utilization, productivity, and welfare) is unknown; however, it is likely to be increased compared with the general population. Research has indicated that heavy drinking in England, which is frequently comorbid with mental health difficulties [13], is estimated to cost the National Health Service (NHS) of the UK £3.5 billion (US $4.4 billion) per year (3.6% of its annual budget) [14].

### Brief Interventions

There is a range of effective intervention options for management and treatment of alcohol misuse categorized as brief interventions, specialist treatment, and less intensive treatments that span the two [15]. Personnel of the UK AF who have left service typically access the same health care system as the general public, and the same interventions are offered to both groups.

Brief interventions for alcohol misuse are a popular management and treatment option used in the UK general population, often provided to individuals scoring 15 or below on the AUDIT [16]. A common theme among these interventions is the goal of improving recognition, targeting the individual’s motivations to reduce their alcohol consumption, and developing coping strategies to control and reduce intake [15-17]. This includes motivational interviewing, cognitive behavioral therapy, behavior self-control training, behavior change, and coping development, all of which are often tailored to the individual by a clinician [15].

Brief interventions aim to raise awareness of the risks associated with alcohol misuse and help individuals reduce their hazardous drinking. Often brief interventions are delivered to individuals who are not seeking help for alcohol misuse from a specialist alcohol service and are delivered in the general community setting (eg, general practitioners, hospital doctors, and nurses). There is a body of research that confirms the efficacy of brief interventions in reducing alcohol consumption and alcohol-related harm for those drinking at a hazardous level in the general population [18-20]. However, little is known about their efficacy in the AF context [19]. Given the shared culture in the military in which alcohol plays a meaningful role, it is important to evaluate the efficacy of brief interventions in this type of population.

### Smartphone-Based Brief Interventions for Alcohol Misuse

The last two decades have seen a proliferation in the use of digital technologies to support brief intervention management and treatment of alcohol misuse in the general public; however, little attention has been paid to the AF community [21-24]. In the late 1990s, interventions were commonly delivered via a computer using CD-ROM–based programs. However, with the advent of the World Wide Web, many new opportunities arose to harness increased reach, provide real-time monitoring, and offer personalized treatment [25-31]. This includes the use of SMS, which has been shown to be effective in encouraging people to change their behavior [32-34].

Over the last 5 years, the mode of intervention delivery has shifted from web- to smartphone-based [35]. Smartphone interventions for alcohol misuse, such as *Drink Less* [24] and *Drink Aware* [36], have several advantages over web-based interventions. These include having a low cost per use, allowing for rapid changes and iterative development, avoiding the stigma associated with receiving help in person, and are highly convenient because they can be used as and when the individual wants (discreetly or openly). However, these smartphone interventions are focused on the general population and do not target individual beliefs, prevailing social contexts, and perceptions of consumption experienced by the AF community [9,37]. Smartphone-based interventions allow users to revisit information about their drinking habits as often as they need to and, thus, have the potential to promote positive behavioral changes [18,38]. Furthermore, there are indications of the potential of smartphone-based interventions being cost effective if found to be efficacious [25,28,29].

Most existing alcohol apps targeted at the general public include self-monitoring (eg, *Drink Less* [24], *Drink Aware* [36], and One You Drinks Tracker [39]), whereby users are encouraged to regularly record and monitor (via visual graphics) their alcohol consumption within an app [24,40]. Self-monitoring (or self-recording) has been found to be associated with improved outcomes and an effective behavior change technique (BCT) for reducing alcohol use. A BCT is defined as a specific component of an intervention designed to change behavior and a putative active ingredient in an intervention [21]. A review of personalized digital interventions for reducing hazardous and harmful alcohol consumption found that providing behavior substitution, problem solving, and providing a credible source were associated with better outcomes, including reductions in alcohol consumption [41]. There are benefits to the use of digital technology for the UK AF community. However, to date, there is no published work that seeks to test a brief intervention alcohol reduction app that is personalized to individual users or targeted to support military veterans.

### Study Aim

The aim of this randomized controlled trial (RCT) is to assess the efficacy of a 28-day brief alcohol intervention delivered via a smartphone app (*Drinks*:Ration) in reducing self-reported weekly alcohol consumption between baseline and 3-month follow-up (day 84) among veterans who drink at a hazardous or harmful level and receive or have received support for mental health symptoms in a clinical setting.

## Methods

### Ethical Approval

This study was approved by the local ethics committee of King’s College London (registration number: HR-19/20-17438) and registered as a clinical trial (registration number: NCT04494594).

### Study Design

This is a two-arm participant-blinded (single-blinded) RCT, which compares a smartphone app (control arm) that includes feedback on baseline self-reported alcohol consumption with a smartphone app (intervention arm) that includes individualized normative feedback, in addition to features designed to enhance participants’ motivation, app interactive feedback, and self-efficacy in modifying their alcohol consumption. We hypothesize that the intervention arm app will be efficacious in reducing alcohol consumption compared with the control arm app. In this study, both the control and intervention arms will be delivered via one smartphone app known as *Drinks*:Ration. Participants in the control arm are given access only to the alcohol consumption feedback on the basis of publicly available health guidance [42] and reminder messaging to consult the feedback. Those in the intervention arm are given full access to the app, which includes all theoretically driven components and messaging (discussed further in the Intervention section). Both arms will be asked to use the app for 28 days. This study is designed such that the control arm structurally resembles the intervention arm but lacks the active ingredients (eg, drinks diary, interactive drinking feedback, and goal setting). This approach was selected to ensure (1) that both groups receive a digital intervention, (2) uniformity and provide relevance to real-world interventions, and (3) that participants are blinded from the study arm they are assigned to. The trial is conducted via the *Drinks*:Ration platform without any need for involvement of the research team, including the collection of informed consent and data collection. The study flow and data collection points are shown in Figure 1.

**Figure 1 figure1:**
[figure not shown]
Study flow diagram. Data collected on day 7/14/21 are required to tailor and personalize the messaging of the Drinks:Ration app for the intervention arm. Primary and secondary outcomes are assessed at day 84, with the outcomes reassessed at day 168 to assess the longer-term benefits of the intervention.

### Study Sample

Participants may have been, or are presently, receiving treatment through Combat Stress. Treatment offered via Combat Stress is for depression, anxiety, and PTSD. However, Combat Stress does not offer alcohol treatment services. The eligibility criteria are as follows:

#### Inclusion Criteria

Participants will be included in the study if they have downloaded the app onto an iOS or an Android device, are aged 18 years or older, live in the United Kingdom, consume 14 UK units (approximately 140 g) of alcohol or more per week as measured using Timeline Follow-back for alcohol consumption (TLFB) [43] at baseline (day 0), provide a mobile phone number, and are veterans of the UK AF. A minimum threshold of 14 UK units of alcohol per week is used in this study to reflect scientific research and UK national guidelines that indicate that regular drinking of more than this threshold risks damage to health [44,45]. It is important to note that in the United Kingdom, individuals are defined as veterans if they have completed a minimum of 1 day paid employment in the UK AF.

#### Exclusion Criteria

Participants will be excluded if they are listed as being *red* risk by Combat Stress, which is determined by the clinical team following an initial assessment and is based on a traffic light system to assess risk, where red indicates an immediate high risk to the individual and/or others. *Red* risk is applied independently of the research team and is used only where participation in the study could impact clinical treatment. The exclusion applies only during the contact list data extraction. Participants will be excluded if they do not have a mobile phone or have not given the Combat Stress consent for contact for research purposes.

A power calculation was performed based on previously reported data from Combat Stress [11,46]. This study requires a sample of 37 participants in each arm, with an 80% power to detect with a probability of 5% mean change in alcohol consumption of 4 UK units (approximately 40 g of alcohol per week, 10 g per unit) between control and intervention arms, at 3-month follow-up (day 84). Four units have been selected based on these 2 criteria: (1) reductions observed in similar studies [4,8,22,24,47] and (2) reductions observed in the feasibility trial of *Drinks*:Ration, which found a 7 UK-unit decrease at week 4. We aim to invite a minimum of 620 veterans to participate in the study to account for a 30% acceptance of invitation and 40% attrition rate.

### Recruitment

This study will recruit participants through Combat Stress (established in 1919), a third-sector charitable organization that provides mental health services, including substance misuse to UK veterans. It is the largest military charity in the United Kingdom in terms of the number of individuals treated, providing both inpatient and outpatient secondary mental health services to veterans and specializing in PTSD. Since 2011, Combat Stress has been funded by the NHS in the United Kingdom to provide a national specialist PTSD clinical service for veterans [48]. Combat Stress facilitates access to eligible participants and jointly with King’s College London oversees any risks that arise as a result of participation in the study. It is important to note that although this study uses a sample of veterans from Combat Stress, it is hoped that *Drinks*:Ration will be useful for the wider veteran community.

Potential participant contact details (postal address and/or email if available) will be extracted from the Combat Stress Patient Management System for those who meet the study eligibility criteria and who have provided consent to be contacted for research purposes. Only those who have had contact with Combat Stress over a 2-year period between January 1, 2018, and December 31, 2019, will be contacted. It is estimated that about 3000 patients with Combat Stress are eligible to be contacted by the research team.

Where contact details are available, eligible participants will be invited to take part via email in the first instance. The first contact will include an explanation of the study, link to the participant information sheet, and instructions on how to download *Drinks*:Ration using a unique quick response (QR) code. Once participants have downloaded the app, they will be invited to report alcohol consumption using TLFB for alcohol consumption [43] for the last 7 days and confirm the military serving status (to validate eligibility). Those meeting the study eligibility criteria will be invited to register an account and complete the baseline questionnaire (day 0).

### Randomization and Blinding

Randomization occurs when a QR code is generated and a unique proxy identifier and participant gender are assigned. At this point, participants are automatically randomized to receive the control or intervention arm (see the Intervention section) and are blinded. Block randomization of size 2 will be used to ensure equal gender distribution across both conditions. The randomization procedure is carried out automatically by the *Drinks*:Ration platform with no human involvement, except to provide a proxy identifier and gender. The research team will be blinded to the randomization of the participant, except for DL, who led the development and will manage the *Drinks*:Ration app throughout the study.

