### Study Withdrawal and Consent

Informed consent will be sought from all participants via the *Drinks*:Ration app before the collection of any personal data, and they will be informed from the outset that they can withdraw from the study at any time. Individual optional consent (screenshots presented in Figure 2) will be sought for access to the GPS location, sending of push notifications, or SMS text messaging. In addition, to promote open science, consent will be sought from participants to share their data anonymously for research purposes. These data will be released upon completion of the study. Only the questionnaire response, remote measurement technology data, and alcohol consumption statistics will be shared. All data will be deidentified, and no personal data will be released. Participants can change optional consents at any time via the *settings* page of the app until analyses are performed at which point data will be extracted and analyzed.

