### Statistical and Data Analysis Plan

Statistical analysis will be performed after completing the data-collection phase. No interim analysis will be undertaken. The threshold for statistical significance will be *P*=.05, and effect sizes will be reported. Descriptive statistics (eg, demographics and response rate) and independent sample *t* tests and chi-square tests will be carried out to explore and identify potential differences between the intervention and control arms at follow-up. An intention-to-treat method will be used for primary outcome analysis such that those who are lost to follow-up will be retained in the primary analysis. Multiple imputation will be performed to estimate missing data, where appropriate. The primary outcome analysis will examine whether there is a statistically significant difference between the intervention and control arms on change in self-reported TLFB UK units consumed (as stated earlier, a difference of 4 UK units will be considered meaningful). Repeated-measures mixed modeling analyses will be conducted to examine the primary hypothesis that those who receive the full functionality of *Drinks*:Ration will report a greater reduction in alcohol consumption compared with control participants from baseline to 3-month follow-up (day 84). For the secondary outcomes, changes in the AUDIT score and WHOQOL-BREF computed quality of adjusted life years will be assessed using repeated-measures mixed modeling. These analyses will be repeated to assess changes between baseline and 6-month follow-up and will serve as a secondary outcome to assess the longer-term impact of the intervention on participants. These analyses will be reported as secondary outcomes.

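### Allocation is made when the QR code is generated, before consent, the drinking check and baseline, so blocks of 2 balance gender among invitees, not participants, and the analysed set is selected after randomisation

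*Protocol article*

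**What the plan says.** Under Randomization and Blinding, the Protocol article states: "Randomization occurs when a QR code is generated and a unique proxy identifier and participant gender are assigned". It adds: "Block randomization of size 2 will be used to ensure equal gender distribution across both conditions".

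Under Recruitment, the first contact explains the study and tells the invitee how to download the app "using a unique quick response (QR) code". The drinking report comes next: "Once participants have downloaded the app, they will be invited to report alcohol consumption using TLFB for alcohol consumption". Registration and baseline are last: "Those meeting the study eligibility criteria will be invited to register an account and complete the baseline questionnaire (day 0". Under Inclusion Criteria, participants must "consume 14 UK units (approximately 140 g) of alcohol or more per week", measured by TLFB at day 0. Under Study Withdrawal and Consent, consent is sought through the app "before the collection of any personal data, and they will be informed from the outset that they can withdraw".

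The sample-size paragraph plans for at least 620 invitations, 30% acceptance and 40% attrition. The Statistical and Data Analysis Plan adopts intention-to-treat for the primary outcome, such that "those who are lost to follow-up will be retained in the primary analysis".

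**The concern.** A unique code has to exist before it can be sent, so every invitee has an arm before responding. Several inclusion criteria (having the app, providing a mobile number, reporting 14 units or more at day 0) cannot be known at that moment. Refusal, non-response and ineligibility, which normally precede randomisation, therefore become losses after it.

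Two things are at stake. The first is a stated property of the design: blocking is said to ensure equal gender distribution across the conditions, but the blocks are formed on a list of which most members never take part. The second is the basis of the primary comparison. Whoever is analysed is a subset chosen after allocation, and the comparison then depends on an assumption that the article does not state: that nothing differs by arm before entry.

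**Working it through.** **Inputs from the Protocol article.** Minimum invited 620; acceptance 30%; attrition 40%; 37 per arm (74 in total); block size 2, read as applied within gender. The share of women is not given and is assumed below. Acceptance is treated as independent between invitees, and everyone who accepts is counted as an entrant. That is generous, because the drinking check removes more people at a rate the article does not give.

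**The plan's own figure.** 74/(0.30 × 0.60) = 411 invitations, not 620. Only 74/(0.30 × 0.40) = 617 comes close, and that uses 40% as retention rather than attrition. This is a separate matter. I use 620 below because it is the stated minimum, and the 70% non-entry rate does not depend on it.

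**Randomised but never entering.** 620 × 0.30 = 186 enter, and 620 − 186 = 434 (70%) do not.

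**What happens to the blocks of 2.** There are 310 pairs.
- Both enter: 0.3² = 0.09, or 27.9 pairs.
- At least one enters: 1 − 0.7² = 0.51, or 158.1 pairs.
- Complete among contributing pairs: 0.09/0.51 = 17.6%.
- Exactly one enters: 2 × 0.3 × 0.7 = 0.42, or 130.2 pairs. So about 130 of the 186 entrants have no partner in the trial.

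**Arm sizes among entrants.** SD of the difference = √(2 × 310 × 0.3 × 0.7) = √130.2 = 11.4. Simple randomisation of 186 people gives √186 = 13.6, so the blocking removes little of the chance variation. The 95% limit is 1.96 × 11.4 ≈ 22. This is the difference between the arms, so the extreme is about 104 v 82.

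**Gender among entrants (assumed share of women, 40,000 simulated trials).**

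| Women among the 620 | Women entering, mean | Arms within 1 woman of each other |
|---|---|---|
| 3% | 5.4 | 56% |
| 5% | 9.6 | 44% |
| 10% | 18.6 | 32% |

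Allocation at entry in blocks of 2 within gender would hold each gender within 1 and the total within 2.

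**Cost in power.** Relative efficiency of 104 v 82 against an equal split: 4 × 104 × 82/186² = 34,112/34,596 = 0.986, a loss of about 1.4%.

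**The case against.** The strongest reply has four parts.

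- **The intention-to-treat statement has its own scope.** It speaks of people lost to follow-up, and someone who never downloaded the app is not lost to follow-up. Keeping all consenting, eligible entrants in their allocated arm is coherent, and a condensed article may leave the naming of that set to the SAP. This stands. A reader might infer that the intention-to-treat claim is false; the text does not go that far. What a SAP cannot change is the timing of allocation, which is fixed here.
- **No bias is shown.** A reader might infer that post-randomisation exclusion biases the result. The documents do not support that. Only one form of invitation is described, participants are said to be blinded, allocation is automated, and the drinking check precedes registration. One gap remains: Table 1 lists different day 0 sign-up messages by arm, and the baseline questionnaire follows registration, so that message could arrive before baseline is complete. It could affect baseline completion, but not the 70% who never accept.
- **Blocks of 2 might seem to reveal a partner's arm.** This carries little weight. Enrolment needs no research staff, the team is blinded apart from the member who manages the app, and most entrants have no partner in the trial.
- **The contact list is already screened.** Recruitment says contact details are extracted for people who meet the eligibility criteria. That cannot include a threshold measured in the app at day 0.

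**Conclusion.** The point holds as a mismatch between a stated property and the procedure, not as a demonstrated bias. The order of events is explicit. Blocks of 2 equalise gender on the invitation list only. Among about 186 entrants, 18% of contributing pairs are complete and the arm difference has an SD of 11.4. Gender imbalance is a chance risk rather than a certainty, and its size depends on the share of women, which the article does not give. An analysis of all 620 randomised is not possible, because about 434 would have no consent, baseline or outcome. The analysed set is therefore selected after randomisation, and it is sound provided that nothing arm-specific precedes entry. These figures assume 620 invitations, 30% independent acceptance in both arms and no loss at the drinking check; such loss would break still more pairs. The loss of power from unequal arms is minor and is not the reason to act.

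**What to change.** Let the QR code carry only the proxy identifier and gender. Trigger the automated allocation inside the app once consent, TLFB eligibility and the baseline questionnaire are complete, blocked within gender, and define intention-to-treat as everyone allocated at that point. This restores the balance claim and makes an analysis of all randomised participants possible. It needs no extra participants or staff. The cost is a change to the allocation trigger, re-testing of an app whose development is reported complete, and revised wording. The change looks small, but the article does not describe the platform in enough detail to confirm that.

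If the build cannot change:
- withdraw the statement that blocking ensures equal gender distribution, or limit it to invitees;
- define the primary set as eligible, consenting invitees who completed baseline before seeing any arm-specific content, and hold the day 0 message until baseline is complete;
- adjust the primary analysis for gender;
- report by arm the numbers invited, downloading, ineligible and completing baseline, so that readers can judge whether pre-entry losses differ.

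The choice has to be made before invitations are sent, because the timing of allocation cannot be repaired afterwards.
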